## Analysis plan

Cancer of the brain, hypophysis,  
corpus pineale and ductus  
craniopharyngealis

Unexposed

Exposed

Spinal cord, cranial nerve and  
other CNS tumours

Unexposed

Exposed

Estimated hazard ratios from Cox regression with time since index date as underlying timescale, stratified by matched set. Adjusted additionally for **systemic treatment for eczema**.

Unadjusted: No adjustment.

Mediation model: Adjusted additionally for time-varying lifestyle-related diseases and **systemic treatment for eczema**.

9. We will repeat the main analysis after starting follow-up at 3 years after index date to limit potential reverse causality. If we see a large change at 3 years, we will also repeat the main analysis by changing start of follow-up to 5 years after index date.

**Table 9. Number of events, accumulated person-time, and HRs for cancer associated with eczema, Denmark. Starting follow-up at 3 years after index date.**

|                          | N | events | P-Y
at
risk | Rate
per
1,000 | Hazard ratio and 99%
confidence interval  |                    |
|--------------------------|---|--------|-------------------|----------------------|----------------------------------------------------------|--------------------|
|                          |   |        |                   |                      | Unadjusted                                               | Mediation
model |
| Any cancer               |   |        |                   |                      |                                                          |                    |
| Unexposed                |   |        |                   |                      |                                                          |                    |
| Exposed                  |   |        |                   |                      |                                                          |                    |
| Lung cancer              |   |        |                   |                      |                                                          |                    |
| Unexposed                |   |        |                   |                      |                                                          |                    |
| Exposed                  |   |        |                   |                      |                                                          |                    |
| Breast cancer            |   |        |                   |                      |                                                          |                    |
| Unexposed                |   |        |                   |                      |                                                          |                    |
| Exposed                  |   |        |                   |                      |                                                          |                    |
| Prostate cancer          |   |        |                   |                      |                                                          |                    |
| Unexposed                |   |        |                   |                      |                                                          |                    |
| Exposed                  |   |        |                   |                      |                                                          |                    |
| Melanoma skin cancer     |   |        |                   |                      |                                                          |                    |
| Unexposed                |   |        |                   |                      |                                                          |                    |
| Exposed                  |   |        |                   |                      |                                                          |                    |
| Keratinocyte skin cancer |   |        |                   |                      |                                                          |                    |
| Unexposed                |   |        |                   |                      |                                                          |                    |
| Exposed                  |   |        |                   |                      |                                                          |                    |
| Lymphoma                 |   |        |                   |                      |                                                          |                    |
| Unexposed                |   |        |                   |                      |                                                          |                    |
| Exposed                  |   |        |                   |                      |                                                          |                    |

---

Multiple myeloma  
 Unexposed  
 Exposed  
 Leukemia  
 Unexposed  
 Exposed  
 Meningioma  
 Unexposed  
 Exposed  
 Cancer of the brain, hypophysis,  
 corpus pineale and ductus  
 craniopharyngealis  
 Unexposed  
 Exposed  
 Spinal cord, cranial nerve and  
 other CNS tumours  
 Unexposed  
 Exposed

---

Estimated hazard ratios from Cox regression with time since index date as underlying timescale, stratified by matched set.

Unadjusted: No adjustment.

Mediation model: Adjusted additionally for time-varying lifestyle-related diseases.

10. We will repeat the main analysis additionally adjusting for immunosuppression (immunosuppressive disorders or drugs).

---

**Table 10. Number of events, accumulated person-time, and HRs for cancer associated with eczema, Denmark. Adjusting additionally for immunosuppression.**

---

|                 | N | events | P-Y
at
risk | Rate
per
1,000 | Hazard ratio and 99%
confidence interval  |                    |
|-----------------|---|--------|-------------------|----------------------|----------------------------------------------------------|--------------------|
|                 |   |        |                   |                      | ‘Unadjusted’                                             | Mediation
model |
| Any cancer      |   |        |                   |                      |                                                          |                    |
| Unexposed       |   |        |                   |                      |                                                          |                    |
| Exposed         |   |        |                   |                      |                                                          |                    |
| Lung cancer     |   |        |                   |                      |                                                          |                    |
| Unexposed       |   |        |                   |                      |                                                          |                    |
| Exposed         |   |        |                   |                      |                                                          |                    |
| Breast cancer   |   |        |                   |                      |                                                          |                    |
| Unexposed       |   |        |                   |                      |                                                          |                    |
| Exposed         |   |        |                   |                      |                                                          |                    |
| Prostate cancer |   |        |                   |                      |                                                          |                    |
| Unexposed       |   |        |                   |                      |                                                          |                    |
| Exposed         |   |        |                   |                      |                                                          |                    |

---

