## Analysis plan

### *Eczema exposed*

- Persons with a diagnosis of atopic eczema (ICD-8: 691; ICD-10: DL20) in the Danish National Patient Registry between 1 Jan 1977 and 10 February 2018.
- We include all primary and secondary diagnoses for eczema from admissions, hospital outpatient clinics and emergency rooms in the Danish National Patient Registry, including ongoing contacts (that is, persons who at the end of study period are in active follow-up in a hospital outpatient clinic).
- Index date = The earliest hospital record for atopic eczema (date of admission or first outpatient appointment).
- Only persons who are born in Denmark and living in Denmark on the index date (i.e. date of first record for eczema).

For the current study, we will further restrict the study population as follows:

- We will exclude eczema patients (together with their matched comparators) identified by an ICD-8 diagnosis recorded together with an additional (“modification”) code indicating that it potentially an uncertain/unverified/working diagnosis (c\_diagmod=1–7).
- We will exclude patients (together with their matched comparators) with inconsistencies in registration of status and residence in the Civil Registration System (recorded as alive but not living in Denmark but without an emigration date), as we assume that these patients are not living in Denmark and thus not eligible.
- To ensure that we have at least 1 year of registration history from included registries (except the prescription registry), we will only include patients (together with their matched comparators) with index date on 1 January 1982 or later. In the subanalysis on severity and in a sensitivity analysis, we restrict to those diagnosed on 1 January 1996 or later in order to ensure one year of registration history in all databases.
- To ensure at least 1 year of follow-up after start of eligible follow-up (available until 30 June 2017), we will include eczema patients until 30 June 2016.
- We will exclude eczema patients (together with their matched comparators) with a record for any cancer (except non-melanoma skin cancer) before or on index date (see Table 2). That is, we will not only exclude those with history of the cancer outcome of interest. However, in analyses of non-melanoma skin cancer specifically, we will exclude those with previous history of this cancer as well.

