### Follow-up

- Follow-up start: index date.
- Follow-up end: earliest of emigration, death, end of study (30 June 2017) or first-ever cancer diagnosis (when examining specific cancers, patients are thus censored if diagnosed with another individual cancer).
- If a person from the comparison cohort is diagnosed with eczema during follow-up, that person will be censored at time of diagnosis. The person will then contribute to the eczema cohort together with his/her own comparators (this has been accounted for in the sampling done by the Danish Health Data Authority)

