## Analysis plan

3. With time since index date as underlying time scale, we will use stratified Cox regression (conditioning on matched set) to compute unadjusted hazard ratios (99% confidence intervals) to determine associations between eczema and each outcome (that is, comparing eczema patients and the comparison cohort). By stratifying on matched set, the model accounts for birth year, sex and calendar period. We will then fit a “mediation model” additionally adjusting for time-varying lifestyle-related diseases (chronic obstructive pulmonary disease, hyperlipidemia, hypertension, alcohol-related conditions, ischemic heart disease, hospital-diagnosed obesity and type II diabetes). If sufficient power, we will adjust for the lifestyle-related diseases as individual variables.

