## Analysis plan

---

|                                                                                     |
|-------------------------------------------------------------------------------------|
| Exposed                                                                             |
| Leukaemia                                                                           |
| Unexposed                                                                           |
| Exposed                                                                             |
| Meningioma                                                                          |
| Unexposed                                                                           |
| Exposed                                                                             |
| Cancer of the brain, hypophysis,
corpus pineale and ductus
craniopharyngealis |
| Unexposed                                                                           |
| Exposed                                                                             |
| Spinal cord, cranial nerve and
other CNS tumours                                 |
| Unexposed                                                                           |
| Exposed                                                                             |

---

Estimated hazard ratios from Cox regression with time since index date as underlying timescale, stratified by matched set.

Unadjusted: No adjustment.

Mediation model: Adjusted additionally for time-varying lifestyle-related diseases.

4. For the atopic eczema cohort, we will make a plot of the cumulative incidence function by age for overall and specific cancers (lung, breast, prostate, lymphoma, leukemia, multiple myeloma, CNS cancers, melanoma and keratinocyte cancer) non-parametrically. This will be done for the unadjusted model.
5. We will assess the assumption of proportional hazards model in all the primary analysis models through Schöenfeld residual plots.

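### The trigger for the 5-year start of follow-up (item 9) measures the early bias already removed, not the bias left after year 3, so it can stop while bias remains

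*Protocol*

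**What the plan says.** The main analysis has no lag (Follow-up section: "Follow-up start: index date"). Follow-up ends at the "earliest of emigration, death, end of study (30 June 2017) or first-ever cancer diagnosis". Patients are eligible "with index date on 1 January 1982 or later", so the longest possible follow-up is about 35.5 years. Under Statistical analyses, item 3, each Cox model gives one HR over the whole of that time, with a 99% confidence interval.

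Reverse causality is handled in Sensitivity analyses, item 9: "We will repeat the main analysis after starting follow-up at 3 years after index date to limit potential reverse causality". This 3-year start is unconditional, and Table 9 lists 12 outcomes under two models. The 5-year start is conditional: "If we see a large change at 3 years, we will also repeat the main analysis by changing start of follow-up to 5 years" after the index date. No amount, outcome or model is attached to the word large.

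The only other look at HRs that vary with time is item 5: "We will assess the assumption of proportional hazards model in all the primary analysis models", using Schoenfeld residual plots. No consequence is attached to the plots, and they play no part in the 5-year decision. No table reports HRs by time since index.

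**The concern.** A longer lag is needed when an early excess of cancer diagnoses continues past year 3. The trigger looks at something else: the gap between the HR from index and the HR from year 3. That gap reflects events in years 0-3, which the 3-year start has already dropped. An excess that stops at year 3 and one that runs on to year 5 can produce gaps of similar size, and only the second calls for the 5-year start. Long follow-up adds to the difficulty, because both HRs rest mostly on the same later events and even a sizeable early excess is diluted in each.

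Item 9 is the only analysis that the protocol assigns to reverse causality. If the rule stops wrongly, the 3-year HR is the last figure reported, some bias is still in it, and no 5-year figure exists to show this. Because the threshold is open, the decision would also be made after the results have been seen.

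**Working it through.** The protocol has no figure to reproduce here: no event counts, no expected bias and no threshold. The checks test the logic of the rule under stated assumptions. In both, the true HR is 1 and an early bias HR, b, acts from the index date.

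**Check A: long follow-up with most events late.** Let s1 be the share of expected events in years 0-3 and s2 the share in years 3-5. The assumed shares are s1 = 0.115, 0.134, 0.148 and s2 = 0.077, 0.086, 0.093. They stand for three index-age mixes (mostly children to mostly adults), with index dates spread evenly over 1982 to June 2016 and cancer hazard rising 8% per year of age. They also depend on how deaths thin the older person-time; with no deaths allowed for, s1 falls to about 0.06. The overall HR is approximated by observed over expected events:

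- bias ends at year 3: HR0 = 1 + (b - 1) x s1, and HR3 = 1
- bias ends at year 5: HR0 = 1 + (b - 1) x (s1 + s2), and HR3 = 1 + (b - 1) x s2 / (1 - s1)
- change seen by the rule = 1 - HR3 / HR0

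For the first mix with b = 1.5 and bias to year 5: HR0 = 1 + 0.5 x 0.192 = 1.096; HR3 = 1 + 0.5 x 0.077 / 0.885 = 1.044; change = 1 - 1.044 / 1.096 = 4.8%.

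| b | s1 / s2 | Ends year 3: HR0, HR3, change | Ends year 5: HR0, HR3, change |
|---|---|---|---|
| 1.5 | 0.115 / 0.077 | 1.058, 1.000, 5.4% | 1.096, 1.044, 4.8% |
| 1.5 | 0.134 / 0.086 | 1.067, 1.000, 6.3% | 1.110, 1.050, 5.4% |
| 1.5 | 0.148 / 0.093 | 1.074, 1.000, 6.9% | 1.121, 1.055, 5.9% |
| 2.0 | 0.115 / 0.077 | 1.115, 1.000, 10.3% | 1.192, 1.087, 8.8% |
| 2.0 | 0.134 / 0.086 | 1.134, 1.000, 11.8% | 1.220, 1.099, 9.9% |
| 2.0 | 0.148 / 0.093 | 1.148, 1.000, 12.9% | 1.241, 1.109, 10.6% |

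Within a row the two changes differ by 0.6 to 2.3 percentage points. Yet the left column has nothing left to find after year 3, while the right column still carries 4-6% (b = 1.5) or 9-11% (b = 2.0).

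**Check B: a different set-up.** Maximum follow-up F = 20 years, even staggered entry, flat baseline hazard, and the log HR averaged over events. The share of events by time T is S(T) = 1 - (1 - T/F)^2, so S(3) = 0.2775, S(5) = 0.4375, S(7) = 0.5775 and S(10) = 0.75. With bias to time T and a lag of L years (L no later than T), HR_L = b^[(S(T) - S(L)) / (1 - S(L))]; for L later than T it is 1. For b = 1.5:

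| Bias lasts to | HR0 | HR3 | HR5 | 0-to-3 change |
|---|---|---|---|---|
| 3 years | 1.119 | 1.000 | 1.000 | -10.6% |
| 5 years | 1.194 | 1.094 | 1.000 | -8.4% |
| 7 years | 1.264 | 1.183 | 1.106 | -6.4% |
| 10 years | 1.355 | 1.304 | 1.253 | -3.8% |

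For a flat bias the trigger is strongest where the 5-year start adds nothing, and it weakens as the bias lasts longer. Under a 10% cut-off (my assumption), the rule would run year 5 for the bias that ended at year 3 and stop for the one that ended at year 5, with HR3 still 1.09.

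**Where the rule works better.** In the same set-up with b = 2.0, bias to year 3 gives 17.5% and bias to year 5 gives 13.9%, so a 10% cut-off triggers in both. A fading bias with b = 2.0 and a 3-year half-life gives 9.8%, or 13.9% if F = 10 years.

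**Where dilution dominates.** With F = 35 years, hazard rising 7% a year and b = 1.5, bias to year 3 moves the HR from 1.028 to 1.000 (2.7%), and bias to year 5 from 1.048 to 1.022 (2.5%). Both changes are small.

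**The case against.** A reader might infer that any bias outlasting 3 years leaves little change, so that the rule stops whenever the longer lag is needed. The documents and the arithmetic do not support that. In Check A most of the smallness comes from dilution over long follow-up, and a bias that ends at year 3 looks almost as small. With a bias to year 5, about 55% of the apparent excess disappears on lagging (for example from 0.096 to 0.044), which an analyst could reasonably call large. A strong or fading bias can trigger the rule. Conversely, a flat bias well past year 5 survives the 5-year start too (1.253 in the 10-year case), so that start is no complete remedy.

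Other points in the plan's favour also stand. The 3-year start is unconditional and covers every outcome in Table 9. The stated purpose is to limit reverse causality, not to exclude it. The residual plots use time since index and could show a falling HR. A numerical threshold could be set in an analysis plan that is not at hand.

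A reader might also think first of lymphoma mistaken for eczema, or of slow-growing cancers. The protocol makes neither argument, and its outcome table removes cutaneous lymphoma codes from the any-cancer and lymphoma outcomes. The point does not rest on them.

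What the objection does not answer is the choice of criterion. Any cut-off on the 0-to-3-year change, wherever it is written down, still measures what has been removed.

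**Conclusion.** The point holds in limited form. The condition in item 9 is not a valid test of whether 3 years is long enough, and it can end the check while bias remains. On the Check A shares, an early HR of 1.5 gives a change of about 5-7% if it ends at year 3 and about 5-6% if it ends at year 5, with 4-6% still in the 3-year HR in the second case. All sizes depend on assumed event shares, bias size and bias shape. What carries across the flat-bias examples is that a bias to year 5 changes the HR less than a bias to year 3 does, and often by a similar amount. Whether the rule would actually stop in this study cannot be known without the event data and a cut-off. This is a worthwhile, inexpensive improvement to one sensitivity analysis; the primary HRs are not affected.

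**What to change.** Delete the condition in item 9 and report both the 3-year and the 5-year start for all Table 9 outcomes. Add HRs by time since index, for example 0-<3, 3-<5 and >=5 years, from the same Cox model stratified on matched set with an eczema-by-period term, each with its 99% interval. Read reverse causality from the early-period HRs against the HR from year 5 on; an excess that lasts well beyond year 5 would then at least be visible as an HR that does not fall. The same table gives the residual plots in item 5 a stated follow-on.

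The cost is a wording change and one extra table from data already held. Period-specific HRs will have wider intervals than the overall HR, and sparse outcomes would fall under the plan's existing rule against publishing results with fewer than 20 events.

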## Analysis plan

---

|                                                                                     |
|-------------------------------------------------------------------------------------|
| Melanoma skin cancer                                                                |
| Unexposed                                                                           |
| Exposed                                                                             |
| Keratinocyte skin cancer                                                            |
| Unexposed                                                                           |
| Exposed                                                                             |
| Lymphoma                                                                            |
| Unexposed                                                                           |
| Exposed                                                                             |
| Multiple myeloma                                                                    |
| Unexposed                                                                           |
| Exposed                                                                             |
| Leukemia                                                                            |
| Unexposed                                                                           |
| Exposed                                                                             |
| Meningioma                                                                          |
| Unexposed                                                                           |
| Exposed                                                                             |
| Cancer of the brain, hypophysis,
corpus pineale and ductus
craniopharyngealis |
| Unexposed                                                                           |
| Exposed                                                                             |
| Spinal cord, cranial nerve and
other CNS tumours                                 |
| Unexposed                                                                           |
| Exposed                                                                             |

---

Estimated hazard ratios from Cox regression with time since index date as underlying timescale, stratified by matched set.

Unadjusted: Adjusted additionally for **immunosuppression**.

Mediation model: Adjusted additionally for time-varying lifestyle-related diseases **and immunosuppression**.

11. We will repeat the main analysis additionally adjusting for use of **oral corticosteroids**. We will define use as a time-updated never/ever variable. Thus, individuals classified as exposed if they ever have a prescription for an oral corticosteroid, with status changing at the first prescription for an oral corticosteroid.

---

**Table 11. Number of events, accumulated person-time, and HRs for cancer associated with eczema, Denmark. Adjusting additionally for oral glucocorticoids.**

---

| N | events | P-Y
at
risk | Rate
per
1,000 | Hazard ratio and 99%
confidence interval  |                    |
|---|--------|-------------------|----------------------|----------------------------------------------------------|--------------------|
|   |        |                   |                      | ‘Unadjusted’                                             | Mediation
model |

---

---

|                                  |
|----------------------------------|
| Any cancer                       |
| Unexposed                        |
| Exposed                          |
| Lung cancer                      |
| Unexposed                        |
| Exposed                          |
| Breast cancer                    |
| Unexposed                        |
| Exposed                          |
| Prostate cancer                  |
| Unexposed                        |
| Exposed                          |
| Melanoma skin cancer             |
| Unexposed                        |
| Exposed                          |
| Keratinocyte skin cancer         |
| Unexposed                        |
| Exposed                          |
| Lymphoma                         |
| Unexposed                        |
| Exposed                          |
| Multiple myeloma                 |
| Unexposed                        |
| Exposed                          |
| Leukemia                         |
| Unexposed                        |
| Exposed                          |
| Meningioma                       |
| Unexposed                        |
| Exposed                          |
| Cancer of the brain, hypophysis, |
| corpus pineale and ductus        |
| craniopharyngealis               |
| Unexposed                        |
| Exposed                          |
| Spinal cord, cranial nerve and   |
| other CNS tumours                |
| Unexposed                        |
| Exposed                          |

---

Estimated hazard ratios from Cox regression with time since index date as underlying timescale, stratified by matched set.

Unadjusted: Adjusted additionally for **oral glucocorticoids**.

Mediation model: Adjusted additionally for time-varying lifestyle-related diseases **and oral glucocorticoids**.

12. We will repeat the main analysis after not censoring unexposed persons who are diagnosed with eczema. Thus, after diagnosis of eczema, unexposed persons will contribute to both unexposed and exposed cohorts (to avoid potential informative censoring by eczema).

**Table 12. Number of events, accumulated person-time, and HRs for cancer associated with eczema, Denmark. Analysis without censoring at eczema diagnosis.**

|                                                                                     | N | events | P-Y
at
risk | Rate
per
1,000 | Hazard ratio and 99%
confidence interval  |                    |
|-------------------------------------------------------------------------------------|---|--------|-------------------|----------------------|----------------------------------------------------------|--------------------|
|                                                                                     |   |        |                   |                      | Unadjusted                                               | Mediation
model |
| Any cancer                                                                          |   |        |                   |                      |                                                          |                    |
| Unexposed                                                                           |   |        |                   |                      |                                                          |                    |
| Exposed                                                                             |   |        |                   |                      |                                                          |                    |
| Lung cancer                                                                         |   |        |                   |                      |                                                          |                    |
| Unexposed                                                                           |   |        |                   |                      |                                                          |                    |
| Exposed                                                                             |   |        |                   |                      |                                                          |                    |
| Breast cancer                                                                       |   |        |                   |                      |                                                          |                    |
| Unexposed                                                                           |   |        |                   |                      |                                                          |                    |
| Exposed                                                                             |   |        |                   |                      |                                                          |                    |
| Prostate cancer                                                                     |   |        |                   |                      |                                                          |                    |
| Unexposed                                                                           |   |        |                   |                      |                                                          |                    |
| Exposed                                                                             |   |        |                   |                      |                                                          |                    |
| Melanoma skin cancer                                                                |   |        |                   |                      |                                                          |                    |
| Unexposed                                                                           |   |        |                   |                      |                                                          |                    |
| Exposed                                                                             |   |        |                   |                      |                                                          |                    |
| Keratinocyte skin cancer                                                            |   |        |                   |                      |                                                          |                    |
| Unexposed                                                                           |   |        |                   |                      |                                                          |                    |
| Exposed                                                                             |   |        |                   |                      |                                                          |                    |
| Lymphoma                                                                            |   |        |                   |                      |                                                          |                    |
| Unexposed                                                                           |   |        |                   |                      |                                                          |                    |
| Exposed                                                                             |   |        |                   |                      |                                                          |                    |
| Multiple myeloma                                                                    |   |        |                   |                      |                                                          |                    |
| Unexposed                                                                           |   |        |                   |                      |                                                          |                    |
| Exposed                                                                             |   |        |                   |                      |                                                          |                    |
| Leukemia                                                                            |   |        |                   |                      |                                                          |                    |
| Unexposed                                                                           |   |        |                   |                      |                                                          |                    |
| Exposed                                                                             |   |        |                   |                      |                                                          |                    |
| Meningioma                                                                          |   |        |                   |                      |                                                          |                    |
| Unexposed                                                                           |   |        |                   |                      |                                                          |                    |
| Exposed                                                                             |   |        |                   |                      |                                                          |                    |
| Cancer of the brain, hypophysis,
corpus pineale and ductus
craniopharyngealis |   |        |                   |                      |                                                          |                    |
| Unexposed                                                                           |   |        |                   |                      |                                                          |                    |
| Exposed                                                                             |   |        |                   |                      |                                                          |                    |

